| Technical Summary (Max. 300 words) *Background*  The population is ageing and consequently, the number of people living with age-related chronic conditions is increasing. Polypharmacy (five or more prescribed medications) is common in older people and is associated with an increased risk of adverse drug reactions. Preventative medications, such as those used to manage blood pressure and cholesterol, are common in polypharmacy and often require large numbers of people to be treated to prevent a small number of cardiovascular disease (CVD) events. This leaves many individuals on drugs of little benefit, some of whom may be susceptible to side effects such as falls, kidney problems and muscle pain.  *Aims*  This proposal aims to quantify the harms of cardiovascular prevention medication, and the characteristics of those people most likely to suffer them. This research is one part of a larger research programme to develop a clinical decision tool which estimates an individual’s likelihood of benefiting or suffering harm from treatment.    *Methods*  Aim 1: Derive prognostic models for an individual’s risk of adverse events associated with cardiovascular prevention treatment (antihypertensives, statins and antiplatelets) using data from the CPRD GOLD. Adverse event outcomes will include falls (antihypertensives), myopathy (statins) and bleeding (antiplatelets).  Aim 2: Externally validate each model using data from the CPRD Aurum.  Aim 3: Use causal inference methods (propensity score matching, instrumental variable analysis) to examine whether modification of treatment could have an important impact on the risk of adverse events. |

| Outcomes to be measured **Primary outcomes** - Falls; Myopathy/muscle pain; Intracerebral haemorrhage  **Secondary outcomes** – Fracture; Syncope; Hypotension (symptomatic); Acute kidney injury; Electrolyte abnormalities; Gout; Diabetes mellitus; Intracerebral haemorrhage; Cataract; Liver dysfunction; Dementia; Memory problems (including dementia); Gastrointestinal haemorrhage; Dyspnoea; Any adverse event  Specific outcomes will be examined in relation to exposure to either antihypertensives, statins or antiplatelets (details given in section N). |
| --- |

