| Exposures, Outcomes and Covariates This study will examine the overall risk of harm from three types of cardiovascular medication: antihypertensives, statins and antiplatelets. ‘Harm’ will be defined by the outcomes listed in the table below, which will be examined both individually and as a composite outcome. The association between treatment and a positive and negative control outcome will also be examined to check the validity of the treatment effect estimates. Positive controls are outcomes know to be affected by treatment (e.g. cardiovascular disease) and negative outcomes are those known not to be affected by treatment.   \| **Variable** \| **Antihypertensive therapy** \| **Statin therapy** \| **Antiplatelet therapy** \| \| --- \| --- \| --- \| --- \| \| Exposure \| ACE inhibitors  Angiotensin II receptor antagonists  Calcium channel blockers  Thiazides and thiazide-like diuretics  Beta blockers  Alpha blockers  Centrally acting antihypertensives  Vasodilators  Renin inhibitors \| Statins \| Aspirin  Clopidogrel  Dipyridamole  Ticagrelor  Prasugrel \| \| Outcome (hospital admission or death due to) \| Falls  Fracture  Syncope  Hypotension (symptomatic)  Acute kidney injury  Electrolyte abnormalities*  Gout  Any adverse event \| Myopathy/muscle pain  Diabetes mellitus  Intracerebral haemorrhage  Cataract  Liver dysfunction  Dementia  Memory problems (including dementia)  Any adverse event \| Intracerebral haemorrhage  Gastrointestinal haemorrhage  Dyspnoea  Any adverse event \| \| Covariates (predictors of outcome and/or treatment) \| Age, sex, BMI, blood pressure, cholesterol, HbA1c, other prescribed medications, co-morbidities, social deprivation, previous adverse events, frailty and proximity to death. \| \| \|   *Defined as any (hyponatraemia, hypokalaemia, hyperkalaemia, hypomagnesaemia, hypophosphataemia hypercalcaemia or hyperuricemia)  All outcomes will be defined according to diagnostic and/or symptom codes, unless otherwise stated. Further sensitivity analyses will explore the impact of our definition of myopathy and muscle pain, focussing on formal diagnostic codes for myopathy only.  Our PPI engagement suggests some patients are concerned about side effects which will result in having to go to hospital, whilst others are more concerned about chronic conditions which affect their daily quality of life. The primary outcomes of this study will therefore be hospital attendance, defined according to ONS and Basic HES datasets. Sensitivity analyses will explore outcomes defined more broadly using primary care codes as well.  All published outputs from this work will be based on the outcomes as specified in this application. Further work with our patient and public involvement representatives will explore definitions of these outcomes and how they should be incorporated into the final calculators developed as part of the wider programme of work related to this project.  Each model will be derived pragmatically, using coded data routinely available in a primary care setting. Potential predictors will be selected based on previous literature and expert opinion.^30 31 44^ Predictors will be defined by codes in the primary care records, using code lists from previous studies (via [www.clinicalcodes.org](http://www.clinicalcodes.org)). Each model will also incorporate basic patient characteristics, blood pressure level, co-morbidities and frailty, estimated from the electronic frailty index. |

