| Data/ Statistical Analysis **Prognostic modelling**  ***Aim 1 – prognostic model derivation (primary analysis)***  Where feasible and appropriate, flexible parametric survival models will be derived in the CPRD GOLD for each outcome separately. Baseline survival over time will be estimated using the Royston-Parmar approach of restricted cubic splines on the cumulative log hazard scale. In contrast to Cox regression, this allows a smoothed estimate of the baseline survival function to be derived, and the time period of prediction to be varied, facilitating individualised risk prediction. For the primary analysis, a 10-year period of prediction will be considered. Further sensitivity analyses will be conducted examining a 5-year period. Where insufficient data are available, or modelling procedures become prohibitively complex (computationally), simpler approaches such as Cox regression will be considered.  Each drug class (prescribed in the 12 months prior to the index date) will be entered into the model as a binary variable to allow for multiple treatments to be considered in each model. Where appropriate, models will be constructed with all other variables entered as continuous (not categorised) variables, and potential non-linear trends will be examined. Transformations or fractional polynomials will be used if non-linear trends are detected. Where hazard ratios are not proportional, interactions of effects with time will be included. Further interaction terms, identified in an accompanying systematic review, accounting for treatment effects which differ across specific populations may be included. Where appropriate, models will be reduced and candidate predictors selected for inclusion based on p values of association. Time since cohort entry will be used as the underlying time function in each survival model.  In a further analysis, we will extend the modelling process as described above to account for competing risk of death from other causes. This will produce a model that predicts the risk of adverse events from cardiovascular treatment over time, in the real world where individuals might die from other causes and thus prevent cardiovascular treatment adverse events from occurring. We will again use a flexible parametric modelling framework to estimate the sub-distribution hazard and cause-specific cumulative incidence functions.^45^  Missing data will be handled, under a missing at random assumption, using multiple imputation (see below) followed by Rubin’s rules to combine parameter estimates across studies.  Where feasible and appropriate, each model will be internally validated using the bootstrap method, to allow optimism-adjusted estimates of calibration and discrimination performance to be obtained. Adjustment for overfitting will be undertaken using a uniform shrinkage factor identified from bootstrapping, followed by re-estimation of the cumulative baseline sub-distribution hazard function (and thus baseline cumulative incidence function) to maintain overall calibration between observed and predicted risks. Given the large sample size, overfitting is likely to be small (see sample size calculation above). If bootstrapping is computationally infeasible due to the large sample size, then a smaller random sample of the population will be used or alternative internal validation methods employed such as cross validation.  ***Aim 2 – prognostic model validation***  External model validation will be undertaken using data from CPRD Aurum. The accuracy of risk predictions from each model will be assessed with calibration plots and 5 and 10 years, calibration measures (slope, E/O statistics), measures of overall fit (using pseudo-R^2^ estimates) and discrimination measures (C-statistics and D-statistics).  ***Aim 3 – causal inference analysis***  For most of the outcomes described in this proposal, the association and magnitude of effect with treatment is not well defined in randomised controlled trials. We will therefore undertake causal inference work to examine whether modification of treatment could have an important impact on the risk of adverse events using two causal inference methods: propensity score matching and instrumental variable analysis.  For the propensity score analysis, eligible patients will be matched 1:1 at the index date using propensity scores, which indicate the likelihood a patient will be prescribed treatment on the basis of their known (pre-treatment) characteristics and other known information which might influence the decision to treat. Predictors of preventative drug prescription will be explored in a logistic regression model. Matched patients will be compared using the Cox proportional hazards models, but hazard ratios will only be adjusted by factors unbalanced at baseline which are not already included in the propensity score model. Time since cohort entry will be used as the underlying time function in each model.  For the instrumental variable analysis, GP’s previous antihypertensive prescribing preferences will be used as an instrument to predict the likelihood of actual treatment. Risk of adverse events will be estimated in patients attending a GP considered a high prescriber of preventative medication and compared to those attending a GP considered a low prescriber. If the results from the propensity score matching suffer from unmeasured confounding, they will differ from those of the instrumental analysis. If this is the case, these models will be refined with additional factors to achieve better adjustment and matching. Where all approaches provide similar results, we can be more confident that the findings are accurate and reliable.^46^  A similar approach will be applied to secondary outcomes, for example, memory loss which has been hypothesised as being linked with statins^47^ and is a concern of many patients in practice, but there is no evidence to support this association from trials.^48^ We recognise that the evidence base may change for some outcomes over the next few years, and so the need to test the associations between treatment and certain outcomes may change.  *Subgroup and sensitivity analyses*  Where possible and appropriate, analyses of treatment associations will be examined in subgroups of the population. These will include age, sex, baseline blood pressure and cardiovascular risk, by drug type/dose/intensity and past medical history. Subgroup definitions will be agreed by expert opinion or taken from an accompanying systematic review of previous trials, examining the same topic.  Sensitivity analyses will be undertaken examining risk models for outcomes defined according to both hospital and primary care records. We will also explore the impact of our definition of myopathy and muscle pain, focussing on formal diagnostic codes for myopathy only. Models utilising a 5-year follow-up will be examined as a further sensitivity analysis. The primary analyses will examine the association between treatment and outcomes, assuming treatments are not altered or modified in the future. Where possible, sensitivity analyses will examine treatment entered as time varying covariates, and censor patients who have treatments removed or switched following the index date. |

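### The pooled electrolyte outcome counts hypokalaemia and hyperkalaemia as one event, so a harm in one direction can be diluted and, under narrower conditions, masked; component results should be pre-specified beside it

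*Protocol*

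**What the plan says.** In the Protocol, the table under Exposures, Outcomes and Covariates gives electrolyte abnormalities one entry among the antihypertensive outcomes. The footnote reads "Defined as any (hyponatraemia, hypokalaemia, hyperkalaemia, hypomagnesaemia, hypophosphataemia hypercalcaemia or hyperuricemia", so seven diagnoses count as one event. Outcomes to be measured places it among the secondary outcomes: "Fracture; Syncope; Hypotension (symptomatic); Acute kidney injury; Electrolyte abnormalities; Gout".

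The listed outcomes are those "which will be examined both individually and as a composite outcome". Electrolytes are a single entry, so this wording separates them from falls or gout but does not separate the seven diagnoses from each other. The same section adds: "All published outputs from this work will be based on the outcomes as specified in this application".

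Under Data/Statistical Analysis:
- Aim 1: "Each drug class (prescribed in the 12 months prior to the index date) will be entered into the model as a binary variable".
- Aim 3: "Matched patients will be compared using the Cox proportional hazards models".
- Treatment subgroups are formed, among other ways, "by drug type/dose/intensity and past medical history".

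One sensitivity analysis changes which diagnoses count, and it concerns another outcome: "Further sensitivity analyses will explore the impact of our definition of myopathy and muscle pain". The sensitivity analysis that adds primary care codes changes the data source and not the list of diagnoses. None of the four amendments alters the footnote.

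**The concern.** Aim 3 asks whether changing treatment matters for the risk of adverse events, and its results feed a harm calculator. Hypokalaemia and hyperkalaemia are the two tails of one measurement. A treatment that shifts potassium in either direction makes one tail more frequent and the other less frequent. An outcome that counts both returns a mixture of the two effects, and the reader of the hazard ratio cannot see the direction of harm.

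Drug-class terms and drug-type subgroups do not help, because they split the exposure and leave the outcome pooled. A one-way shift is in fact most plausible within a single class. Since published outputs are tied to the outcomes as specified, the protocol as written gives no place for the separate results.

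**Working it through.** **The plan's own figure.** Sample size considerations gives 4,634 events and 88,380 patients for Aim 3 (10% increase, 90% power, alpha 0.05). Freedman's formula with 1:1 groups and a two-sided test gives ((1.10 + 1)/(1.10 − 1))² × (1.960 + 1.2816)² = 441 × 10.507 = 4,634. Assuming 10 years at 0.5% per year, control survival is 0.95 and treated survival 0.95^1.1 = 0.9451. The mean event probability is 0.05243, and 4,634/0.05243 ≈ 88,384 patients. The figure reproduces and is not in dispute.

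**Inputs the documents do not give.** These are the share of each component among untreated events and the effect of treatment on each. All values below are assumptions.

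**Pooled hazard ratio.** For rare events with constant hazards, pooled HR = sum of (component's share of untreated events × component HR). Let the raised potassium part have HR 1.5, the lowered part 1/1.5, and let s be the raised part's share of potassium events. The potassium part then has HR = 1.5s + (1 − s)/1.5. If 40% of all events are other components with HR r, pooled HR = 0.6 × (potassium HR) + 0.4r.

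| s | Potassium part | Pooled, r = 1.0 | Pooled, r = 1.2 |
|---|---|---|---|
| 30% | 0.92 | 0.95 | 1.03 |
| 40% | 1.00 | 1.00 | 1.08 |
| 50% | 1.08 | 1.05 | 1.13 |
| 60% | 1.17 | 1.10 | 1.18 |

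**When the result is null.** With effects h and 1/h and r = 1, the pooled HR is 1 when lowered share/raised share = (h − 1)/(1 − 1/h) = h. The lowered part must therefore be 1.25, 1.5 or 2.0 times as common as the raised part for h = 1.25, 1.5 or 2.0. Above that ratio the pooled HR falls below 1. Below it, the harm is diluted but keeps its sign.

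**Check by a different route.** Take potassium as normally distributed, shift it up by 0.2 SD and recompute the two tails, ignoring other components.
- Untreated tails 3% low and 1% high: high-tail risk ratio 1.67, low-tail 0.62, pooled 0.89.
- Tails 1% and 1%: pooled 1.13.
- Tails 1% low and 2% high: pooled 1.26.

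The pattern is the same: dilution in general, and reversal only when the lowered tail is clearly the larger.

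**Chance of a significant result at 4,634 events.** Power = Φ(|ln HR| × √(4,634/4) − 1.96), with √(4,634/4) = 34.04.
- HR 1.05: Φ(0.0488 × 34.04 − 1.96) = Φ(−0.30) = 38%.
- HR 1.10: Φ(1.28) = 90%.
- HR 0.95: Φ(−0.21) = 42%, for a significant result in the protective direction.

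The 4,634 is a required minimum and not the expected count. With an assumed 20,000 events, power at HR 1.05 is Φ(0.0488 × √5,000 − 1.96) = Φ(1.49) = 93%. More events do not move the pooled value itself.

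**What separate analysis would retain.** A component supplying 10% of 4,634 events (463) has power Φ(0.4055 × √(463/4) − 1.96) = Φ(2.40) = 99% for HR 1.5. At 5% (232 events) it is Φ(1.13) = 87%. For HR 1.25 with 463 events it is Φ(0.44) = 67%.

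**The case against.** The footnote is a clear and reproducible definition of a secondary outcome. The net effect on any electrolyte disturbance is a legitimate question, and if one direction rises while the other falls, a net null is the right answer to it. No passage says that any antihypertensive moves potassium, or which way. The main contrast covers nine drug classes. If these differ in direction, both potassium parts could rise and nothing would cancel. Component breakdowns are also often left to an analysis plan. All of this stands as a limit on strength. What remains is that the protocol fixes the pooled definition itself and ties publication to it, so a net result would appear without the information needed to read it.

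Three stronger readings are tempting and are not supported.

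- A reader might infer that a real harm will cancel or look protective. That needs the lowered component to be sufficiently commoner and the other components to be near null. In the table, two of the four rows stay above 1 even with r = 1.0, and all four do with r = 1.2.
- A reader might infer that the composite of any adverse event suffers the same cancellation. It also contains falls, fracture, syncope, hypotension, acute kidney injury and gout. If electrolytes were 10% of its events and the rest had HR 1.10 (both assumed), moving the electrolyte HR from 1.3 to 1.0 would move the composite from 0.13 + 0.99 = 1.12 to 0.10 + 0.99 = 1.09.
- A reader might call the inclusion of hyperuricaemia an error, since gout is a separate outcome. The footnote lists it openly and no analytic fault follows. Where it sits is a preference.

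**Conclusion.** The concern holds as a risk of dilution, with masking possible under narrower conditions. The pooling is explicit and nothing in the protocol separates the two potassium components. On the assumed effects of 1.5 and 1/1.5, with 40% of events unaffected, a 50% increase in one harm appears as a pooled HR between 0.95 and 1.10. At 1.05 or below, that is less than the 10% increase the protocol itself treats as clinically significant. With the other components at HR 1.2 the range is 1.03 to 1.18.

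These figures rest on assumed shares and effects, a one-way shift in potassium, rare events and constant hazards. They show what the definition permits and do not predict a result. No primary outcome, eligibility rule or sample size is affected, and the effect on the any-adverse-event composite is probably small. This is an inexpensive improvement to a secondary outcome.

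**What to change.** Keep the pooled outcome. State in the outcome-table footnote and in Aim 3 that hyperkalaemia, hypokalaemia and hyponatraemia are also analysed separately as secondary component outcomes, overall and by drug class, and that their hazard ratios are reported beside the pooled one. The statement belongs in the protocol because publication is tied to the outcomes specified there.

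No new data are needed, since the hospital and mortality data already requested define the components. Each component has fewer events and a wider interval, most noticeably for modest effects in rare components, and there are a few more secondary comparisons. Amendment 2 cites computing time as a constraint and appears to tie imputation models to outcomes, so three added outcomes may mean up to three further imputation runs. Under that amendment, the drug-class subgroup analyses would use propensity score adjustment only.
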